### Data storage

All consented participants will be allocated a trial participant number. A REDCap database will be used to record the data, entered by the member of the research team. The data from the database will be used for analysis of the trial and will be archived for a minimum of 15 years. The online questionnaires completed by patients will be directly linked to the REDCap database.

## Discussion

Dichloroacetate (DCA) may be a potential novel non-hormonal treatment for endometriosis-associated pain in women. To date, this is the first study investigating DCA for endometriosis pain and assessing whether it is possible to achieve acceptable recruitment and retention rates. Given that many trials struggle with recruitment and often request extensions or become at risk of closure [23], investigating the feasibility and acceptability of treatments or interventions is of great importance to inform design of future definitive controlled trials [24]. If there are any indicators of problems with feasibility and acceptability affecting recruitment, retention, or safety, those relevant procedures will be revised and modified.

Our sample size of 30 women and 6 months recruitment period would be reasonable to provide a justified information of feasibility, acceptability to methodology (recruitment, retention, treatment, follow-up frequency), compliance rate and response to questionnaires. A key strength of the study is the clear definition of participant’s disease as endometriosis diagnosed via laparoscopy within the past five years (excluding deep endometriosis), and the specific inclusion and exclusion criteria would be reflective to the patient’s eligible to be on DCA in the future RCT based on their suitability for DCA as treatment option.

The questionnaires used to measure the physical and emotional functioning were selected based on the Initiative on Methods, Measurement, and Pain Assessment in Clinical Trials (IMMPACT) recommendations for chronic pain trials which would provide a reflective account on the women’s experiences [15–18]. Although pain scores and satisfaction rates are being used as part of the study protocol, the trial is not designed nor powered for formal analysis of effectiveness. The questionnaire results (e.g. pain score, physical and emotional functioning) from this study will not be carried forward for future studies. However, the nature and number of unanswered questions in the questionnaire can help us to assess suitability of the questionnaires and identify important outcome measures for future study.

This study is limited to examining the feasibility and acceptability of DCA intervention within a single tertiary centre setting and does not examine the feasibility of a multi-centre trial. This study does not assess the willingness of participants to be randomised and therefore cannot estimate the recruitment rate of future RCT but allow estimation of number of eligible patients and estimation of time frame for recruitment and collection of data in future RCT. The results may not be truly representative of all patient demographics due to selection bias as participants are recruitment from a single centre and must be willing to comply with the frequent follow-up visits.

DCA offers promise for a novel, non-hormonal medical therapy for the treatment of endometriosis-associated pain. The success of this study will depend on developing appropriate recruitment strategies. Ideally, we would want to meet both our recruitment and retention targets before consideration of a larger randomised controlled trial. However, Covid-19 social distancing guidelines and the closure of many outpatient gynaecology clinics during the lockdown is making the collection of follow-up data more difficult as patients are less willing to attend non-urgent hospital appointments. Thus, our estimates of both recruitment and retention are likely to be underestimates of these figures under normal circumstances. Nonetheless, this study will still give us an estimate of the lower limit of these figures, which can then be used to inform a future clinical trial comparing the effectiveness of DCA to placebo administration for endometriosis-associated pain.

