### Study design

This is a single site, open-label exploratory study of women with endometriosis.

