### Primary endpoint

The primary endpoint is to determine recruitment and retention rates. Using the information collected from the participant log, we will determine the number of patients recruited from the pool of eligible women and a 50% of 60, 95% CI (36.8–63.2%) recruitment will be deemed acceptable. While a retention rate of 100% would be ideal, we will consider a rate of 80% satisfactory. We will provide an estimate of the proportion and its 95% CI (61.4–92.3%). In addition, we will determine the nature and number of unanswered questions in each questionnaire. We aim to determine whether the trial design will perform well enough in the field to warrant rolling out the study to full trial. All analysis will be carried out in the University of Edinburgh.

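### The Discussion's lower-limit claim for recruitment and retention rests on Covid-19 alone and does not support planning a placebo-controlled trial

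*Protocol article*

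**What the plan says.** All of the reasoning is in the last two paragraphs of the Discussion in the protocol article.

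- **Limitations paragraph.** On randomisation: "This study does not assess the willingness of participants to be randomised and therefore cannot estimate the recruitment rate of future RCT". The same sentence says the study can still inform the number of eligible women and the time frame for recruitment. The paragraph also discloses "selection bias as participants are recruitment from a single centre and must be willing to comply with the frequent follow-up visits".
- **Closing paragraph.** Because of distancing rules and clinic closures, "our estimates of both recruitment and retention are likely to be underestimates of these figures under normal circumstances". The next sentence draws the conclusion, "Nonetheless, this study will still give us an estimate of the lower limit of these figures", and gives its use: "which can then be used to inform a future clinical trial comparing the effectiveness of DCA to placebo administration".

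Two other sections bear on the point. Study design states: "This is a single site, open-label exploratory study of women with endometriosis"; under Intervention every participant is given DCA. Primary endpoint sets the criteria: 50% recruitment, expressed on 60 women with a 95% interval of 36.8–63.2%, and 80% retention, of which it says "We will provide an estimate of the proportion and its 95% CI (61.4–92.3" (in per cent).

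**The concern.** Calling an estimate a lower limit is a claim about direction: the true rate should be at least this high. The article reaches that claim from one influence, the pandemic, and then names a placebo-controlled trial as the user of the figure. Several features that separate the present study from such a trial are either disclosed and then not used (one tertiary centre, selection for willingness to attend, no test of randomisation) or not discussed in this context (open-label treatment, active drug for everyone). Any of these could make the observed rates differ from the RCT's rates, and not necessarily in the direction in which Covid-19 acts.

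The two rates are the primary output of the study, and their purpose is to inform the RCT. If a planning team takes them as a floor, it has no reason to allow for lower uptake or higher attrition when it sets the number of sites, the recruitment period and the dropout allowance.

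**Working it through.** **1. The article's own intervals.** Inputs from Primary endpoint and Sample size: recruitment 50% of 60, so 30/60; retention 80% of the planned 30, so 24/30. The exact (Clopper-Pearson) 95% limits for x out of n are

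- lower = Beta quantile at 0.025 with parameters x and n − x + 1
- upper = Beta quantile at 0.975 with parameters x + 1 and n − x

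| Rate | x/n | Exact 95% limits | Article |
|---|---|---|---|
| Recruitment | 30/60 | 36.8% to 63.2% | 36.8–63.2% |
| Retention | 24/30 | 61.4% to 92.3% | 61.4–92.3% |

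Both reproduce. Wald limits (37.3–62.7% and 65.7–94.3%) and Wilson limits (37.7–62.3% and 62.7–90.5%) do not, so the stated intervals are exact ones.

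**2. Is the point estimate a bound?** With X binomial, the chance of meeting or exceeding a criterion when the true rate lies below it is:

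- P(X ≥ 24 of 30) = 0.16 if true retention is 70%, and 0.35 if it is 75%
- P(X ≥ 30 of 60) = 0.07 if true recruitment is 40%, and 0.26 if it is 45%

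An observed 80% or 50% can therefore exceed the true rate through sampling variation alone. This holds with or without any pandemic effect.

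**3. Does the direction of bias follow?** Let c be the factor by which Covid-19 multiplies a rate, and w the factor by which moving from open-label active treatment to a randomised placebo-controlled trial multiplies it. Then

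RCT rate = observed rate × w / c,

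and the observed rate is a floor only if w is at least c. The documents give neither factor. The ranges below are assumptions for illustration.

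| Rate | Observed | Assumed c | Assumed w | Lowest implied | Highest implied |
|---|---|---|---|---|---|
| Recruitment | 50% | 0.7 to 1.0 | 0.6 to 1.0 | 0.50 × 0.6/1.0 = 30% | 0.50 × 1.0/0.7 = 71% |
| Retention | 80% | 0.85 to 1.0 | 0.8 to 1.0 | 0.80 × 0.8/1.0 = 64% | 0.80 × 1.0/0.85 = 94% |

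Both ranges straddle the observed value. The lower-limit conclusion uses c and leaves w out.

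**4. The two paragraphs side by side.** For recruitment, the limitations paragraph says that the RCT's rate cannot be estimated because willingness to be randomised is untested. That amounts to saying w is unknown. The closing paragraph then supplies a recruitment limit to inform a placebo-controlled trial. If w is unknown, the RCT's rate can be neither estimated nor bounded from this study. For retention there is no matching disclaimer, so the fault there is an unsupported inference and not a contradiction.

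**The case against.** The strongest reply is about wording. The sentence before the conclusion speaks of rates under normal circumstances, so the limit literally refers to this design outside lockdown. A reader might infer that the article claims a floor for the RCT's own rates. It does not say so; the RCT is only to be informed. This reply stands and narrows the point, but it does not remove it: the stated use is still a placebo-controlled trial, and even for this design a sample proportion is not a bound.

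A reader might also say that the article ignores its limitations. That is too strong. Single centre, selection and untested randomisation are all disclosed; what is missing is their use in the conclusion. Nor do the documents show that these features push the rates upward. Frequent visits may lower uptake while raising retention among those who enrol. Active drug with known side-effects, and freedom to stop it, might lower retention relative to a placebo arm, in which case w could exceed 1. This too stands, and it is why the point is stated as unknown direction and not as upward bias.

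A third reply is that the article already promises a 95% interval for retention and keeps its 50% and 80% criteria. That is correct, and readers will have the interval. But the Discussion does not refer to it when it speaks of a lower limit.

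**Conclusion.** The point holds in a limited form. The lower-limit conclusion is reached from Covid-19 alone, omits limitations that the article itself sets out, and for recruitment conflicts with its statement about the RCT rate. The intervals in the article show how far a sample proportion is from a floor: the lower limits are 36.8% for an observed 50% and 61.4% for an observed 80%. The size of the net bias for a placebo-controlled trial cannot be derived from the documents. The ranges of 30–71% and 64–94% rest wholly on assumed factors and show only that the direction is open.

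Two stronger readings should be set aside.

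- *Enrolment shortfall as a measure of the bias.* With an assumed 100 evaluable women, 100/0.80 = 125 would be enrolled at the point estimate and 100/0.614 = 163 at the lower confidence limit, or 30% more. This is sampling error at n = 30; it would be the same without any pandemic and does not measure the effect of open-label treatment. The figure of 100 is not in the article, and nothing there says the RCT would be sized on the point estimate.
- *Attendance as the wrong definition of retention.* Visits also include blood sampling and neurological examination, and the pain rating scale is on paper only, so online questionnaires do not replace attendance. Counting attendance is defensible.

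This concerns the interpretation of the primary results. The endpoints, criteria and sample size of the present study are unaffected.

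**What to change.** 1. **Wording.** Replace the lower-limit sentence with text to this effect: *The observed rates may underestimate those of this open-label single-arm design outside the pandemic. As a guide to a placebo-controlled trial they are subject to further influences, including untested willingness to be randomised, and the net bias is of unknown direction.*
2. **Planning value.** Name the lower 95% confidence limit of each rate as the cautious value to carry into RCT planning, and say that it covers sampling error only, not the change of design.
3. **Split by clinic closure.** Report recruitment and retention separately before and after closure. For recruitment, the screening log already records the date of clinic attendance. For retention, classify each woman by the date on which her week-12 visit was due, counted from day 1, because those who did not attend have no visit date.

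**Cost.** No new data are needed, and no endpoint or sample size changes. The conclusion becomes less favourable, and the split estimates will be imprecise. If the 30 women divided evenly, for example, 12/15 retained would have an exact 95% interval of 51.9% to 95.7%, against 61.4% to 92.3% for 24/30. The split is therefore descriptive and cannot settle how much Covid-19 mattered.

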## Data Availability

Data sharing is not applicable to this article as no datasets were generated or analysed during the current study.

## Abbreviations

ACCORD: The academic and clinical central office for research and development
AEs: Adverse events
ASRM: American Society of Reproductive Medicine
BFI: Brief fatigue inventory
CRF: Case report form
CTIMP: Clinical trial of an investigational medicinal product
DCA: Dichloroacetate
GCP: Good Clinical Practice
HPMC: Human peritoneal mesothelial cell
IMMPACT: Initiative on methods, measurement, and pain assessment in clinical trials
IQR: Interquartile range
NHS: National Health Service
NRS: Numerical rating scale
PDK: Pyruvate dehydrogenase kinase
RCT: Randomised controlled trial
SAEs: Serious adverse events
